## Abstract

**Background:**

Suicidal and non-suicidal self-injurious behaviors are among the leading causes of death and injury in adolescents and youth worldwide. Mobile app development could help people at risk and provide resources to deliver evidence-based interventions. There is no specific application for adolescents and young people available in Spanish. Our group developed CALMA, the first interactive mobile application with the user in Spanish, which provides tools based on Dialectical Behavioral Therapy to manage a crisis of suicidal or non-suicidal self-directed violence with the aim of preventing suicide in adolescents and youth.

**Methods:**

To test the effectiveness, safety and level of engagement of the CALMA app in people aged 10 to 19 who are treated in mental health services of two public hospitals, we will conduct a parallel-group, two-arm randomized controlled trial. Participants will be assessed face-to-face and *via* video call at four timepoints: day-0 (baseline), day-30, day-60, and day-90. A total of 29 participants per group will be included. Change in the frequency of suicidal and non-suicidal self-injurious behaviors will be compared between groups, as well as the level of emotional dysregulation, level of app engagement and time of psychiatric admission during the follow-up period.

**Discussion:**

This study is particularly relevant to young people given their widespread use of mobile technology, while there are currently no available smartphone app-based self-guided psychological strategies in Spanish that attempt to reduce suicidal behavior in adolescents who are assisted in the public health sector from low and middle-income countries in Latin America.

**Clinical trial registration:**

https://clinicaltrials.gov/, NCT05453370.

## Introduction

Suicidal behaviors are among the leading causes of death and injury worldwide. Over 700,000 people die by suicide every year (1). For every suicide, more than 30 people attempt suicide (2), and the lifetime prevalence of suicide attempts (SA) among the general population is approximately 2.7% (3). The magnitude of the problem is even higher if we consider the prevalence of suicidal ideation (SI), being estimated at 8.3% in the Southern Cone of Latin America (4). Altogether, these data suggest that the impact of suicidal thoughts and behavior is a significant public health problem around the world (5). Regarding Non suicidal self-injury (NSSI) rates are also high, particularly among adolescents (6), with approximately 20% of high school students reporting at least one episode of NSSI in the past 12 months (7). This is in particular importance, as NSSI is a significant risk factor for suicidal behaviors (8, 9).

The suicide mortality rate Argentina is 7.47 per hundred thousand inhabitants (10). Lately, there was a gradual and sustained growth in the suicide rate in individuals between 15 and 24 years of age (10). In 2019, of the total of 3,297 deaths by suicide, 868 deaths occurred in those between 15 and 24 years of age, representing the second cause of death (after traffic accidents) (10). In adolescents (people between 10 and 19 years old according to the WHO) a total of 459 deaths by suicide occurred in that year (10). This epidemiological transition observed in Argentina coincides with what has been reported internationally and confronts us with a new challenge.

The evidence on the efficacy and effectiveness of suicide prevention strategies, such as Dialectical Behavioral Therapy (DBT), have been described (11–14). Indeed, DBT prioritizes suicidal behavior as the primary goal of treatment. In a meta-analysis of 18 RCTs, DeCou et al. demonstrated a significant pooled effect for DBT compared to control groups for self-directed violence (suicidal and NSSI behavior; *d* = −0.324, 95% CI = −0.471 to −0.176); however, there was no significant pooled effect of DBT for suicidal ideation (15). A more recent review, which evaluated the benefits and harms of psychological therapies for borderline personality disorder, identified DBT as having the largest number of primary trials, finding it to be the most effective psychotherapy at reducing self-harm (SMD-0.28, 95% CI-0.48 to-0.7; 7 trials, 376 participants) compared to TAU (16). Furthermore, in adolescents, 19 weeks of DBT was associated with a significantly lower frequency of self-harm episodes and suicidal ideation at post-treatment, 1 year, and 3 years follow-up (17, 18). In addition, some studies with similar results have added data regarding the feasibility of implementing DBT in adolescents, even at a community level, a necessary hallmark of the program (19, 20). Recently, a meta-analysis by Witt et al. concluded that there was a lower recurrence rate of self-harm (intentional self-harm) for adolescent DBT (30%) compared with treatment as usual, enhanced usual care, or alternative psychotherapy (43%) in repeated post-intervention self-harm in four trials (OR 0.46, 95% CI 0.26 to 0.82; *N* = 270; *k* = 4; high-certainty evidence) (21).

Despite this, and due to the short time to intervene in the suicidal process (22, 23), a crucial aspect of their effectiveness in daily practice is accessibility. This is why, beyond employing effective interventions to prevent suicide, they must be quickly available at the time of crisis.

### Rationale

There has been rapid growth in the development and use of digital intervention technologies (24). New platforms to provide evidence-based interventions, universally, economically, and quickly are needed (25, 26). Smartphones appear to be a good alternative considering the high penetration of these devices locally (26), and the development of mobile applications (apps) to prevent suicidal behavior might could support individuals at risk (27, 28) and provide resources to deliver evidence-based interventions (29). Several developments have occurred, and protocols for effectiveness evaluation have also been published (30–40), but few included descriptive reports on the development process and feasibility (36, 41–43).

Since the app review by Larsen in 2016 (44), nearly twice as many apps designed to reduce suicide have been introduced in app stores (45). Most of the apps available provide information about suicidal behavior/NSSI or general information about mental health. In general, they include functions that allow interaction with the user to help manage the crisis, typically using two types of suicide prevention strategies: (a) providing emergency resources to the user (non-existent or inaccurate suicide crisis helpline phone numbers in a few of them (46); (b) providing management/reduction of (acute) general or suicidal/NSSI urges and behavior, with a focus on developing a safety plan or using some type of coping strategy (45–48). Unfortunately, several mobile apps targeting suicidal behavior have not employed evidence-based treatment approaches (44, 49). Furthermore, to our knowledge, no specific app for adolescents and young people is available in Spanish (only one app, Prevensuic, is in Spanish, but it is not interactive, it does not present tools or coping skills, and it is not specifically targeting adolescent) (35, 50). Our group developed CALMA (the Spanish word for “calm”), the first user-interactive mobile app in Spanish. CALMA provides evidence-based tools to manage a suicidal or non-suicidal self-directed violence crisis with the goal of preventing death by suicide (51). CALMA also interacts with the user between crises by promoting activities that reduce their vulnerability to future crises, and providing psychoeducation about suicide and its prevention (51).

Our research group carried out a pilot cluster randomized controlled trial with 4 weeks of follow-up that provided initial evidence on the safety and acceptability of the app for reducing self-injurious thoughts and behaviors when used as an adjunct to conventional DBT therapy (52). Being the first pilot study, this was carried out in a group of patients already under a DBT treatment program in a private clinical setting. Six DBT Skills Training groups were randomized to the intervention (DBT + CALMA) or control (DBT alone). Although efficacy was not the main outcome, since it was a pilot study, the results showed a high probability of decreased suicidal ideation, suicidal plan, suicidal gesture (or threat), thoughts about Non-Suicidal Self-Injury (NSSI), and NSSI in the group receiving CALMA app. Moreover, CALMA showed good acceptability as an adjunct to therapy targeting suicidal and non-suicidal self-injury behaviors measured with the User Experience Questionnaire in its short version (UEQ-s) (52).

Since the pilot study was not powered for efficacy, and based on these encouraging initial findings, in this project we propose to scale the intervention to a larger group of patients, focus it on adolescents, and include public hospitals not specialized in DBT.

## Objectives

### General objective

To evaluate the efficacy, safety and acceptability of CALMA, a suicide prevention app for smartphones, to reduce the frequency of self-injurious thoughts and behaviors in adolescents who are assisted in a Mental Health service at two Public hospitals.

### Specific objectives

#### Primary specific objectives

Compare the change in the frequency of self-injurious behaviors in the participants who receive the app with the frequency in those who do not receive the application.

#### Secondary specific objectives

Analyze the frequency of self-injurious thoughts in the participants who receive the application with the frequency in those who do not receive the app.Establish that there is no increase in the frequency of self-injurious thoughts and behaviors in those participants who receive the application compared to the baseline levels at study onset.To explore whether the effectiveness of CALMA in reducing the frequency of self-injurious thoughts and behaviors is mediated by improved emotional regulation.Describe the levels of app engagement by the adolescent participants who used it during this study.To compare the time to psychiatric admission during the follow-up period in the participants enrolled who received the app with those participants who did not receive the app.

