### Sample size

The sample size was calculated using the G*Power 3.1.9.4 statistical software according to the main objective. Considering a confidence level of 95%, a power of 80% and an effect size *d* = 0.85, 25 individuals per group are needed to detect a significant difference in the median frequency of self-injurious behaviors with the two tailed Mann–Whitney U test. Assuming a proportion of lost in the follow-up of 15%, then the study would have to start with 29 individuals per group.

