### Statistical analysis

To describe the sociodemographic characteristics of the patients in the two groups, absolute and relative frequencies (%) will be used for the qualitative variables, and the mean and standard deviation will be used for the only quantitative variable (age) if it presents a normal distribution according to the Shapiro–Wilk test. In case of presenting a non-normal distribution, the median and the interquartile range will be computed.

To compare the sociodemographic characteristics between the groups, the chi-square or Fisher’s exact test will be used for the qualitative variables, and the student’s t-test or the Mann–Whitney U test will be computed for the quantitative variable.

For all patients and at each follow-up moments, the difference between the frequency of each suicidal behavior and the baseline frequency will be calculated. Then it will be evaluated if these differences follow a normal distribution (Shapiro–Wilk test). In this case, the mean differences for each behavior between both groups will be compared using the t-Student test. Otherwise, the medians will be compared with the Mann–Whitney U test. The *p*-values obtained will be corrected according to the Bonferroni criterion.

To assess whether the change in emotional regulation mediates the change in the frequencies of each suicidal behavior, the difference between the value of the DERS scale at the last follow-up and the baseline will be calculated, and the Sobel test will be used on a regression model whose dependent variable will be the difference in the frequency of each behavior and the independent variable will be the treatment. Previously, the probability distribution of the quantitative variables will be evaluated and it will be considered whether it is necessary to carry out any transformation of data to guarantee compliance with the assumptions of the regression model.

Both for the frequencies of the different suicidal behaviors and for the DERS scale, the missing values will be imputed according with the multiple imputation method using chained equations (MICE) with appropriate models for each variable to be imputed, considering sociodemographic characteristics, the hospital of recruitment and the baseline measurements of frequencies and DERS scale as independent variables.

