Regarding acceptability, the UEQ Data Analysis Tool offers a benchmark to classify the application in 5 categories of 6 scales: excellent, good, above average, below average and bad allowing conclusions to be drawn about the relative quality of CALMA compared to other products.^2^

To evaluate and compare the time to readmission in patients enrolled during hospitalization, a Cox regression model will be adjusted, considering the treatment of each patient as the independent variable. For this, the time elapsed from study entry to readmission (event) or to loss of follow-up or final of the study (censoring) will be calculated. In all cases, a value of *p* less than 0.05 will be considered significant. Statistical analysis will be performed with RStudio 1.4.1106.

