## Ethics and dissemination

The present protocol and applied informed consent forms were approved concerning their content and compliance with ethical regulations by the Elizalde Hospital Ethical Committee and the Institutional Committee for the Review of Research Protocols. The study is carried out with principles enunciated in the Declaration of Helsinki. Furthermore, the study will be carried out following the “Law on the Protection of the Rights of Subjects in Health Research” (Law 3,301) and the “Law on the Protection of Personal Data” (Law 25.326) of Argentina. In addition, all rights protection guidelines for human volunteers will be followed.

All researchers participating in the project are trained in research ethics and are familiar with current regulations. Only authorized study personnel will have access to protect the confidentiality of the data in the electronic database where the data is found. The information that will be obtained in the database will not have personal identification; each study participant will be assigned a unique identification code (ID).

The inclusion criteria for the study imply that the patients included in it must have presented some self-injurious behavior the month before the evaluation; therefore, they are high-risk patients. For this reason, they will be receiving treatment by the Mental Health team during the study period. The additional risks for the intervention (the use of the CALMA app) are low for this study, in previous studies we have shown that the app does not increase the risk of suicide.

The results of the planned analyzes will be published in a peer-reviewed journal.

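### The trial sets out to establish that self-injury does not increase in app users, but none of its planned analyses can establish that

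*Protocol article*

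**What the plan says.** Under Secondary specific objectives, the protocol article sets the aim to "Establish that there is no increase in the frequency of self-injurious thoughts and behaviors in those participants who receive the application". The reference point is the same participants' own frequency at entry. The contrast is therefore within the app arm, before against after, and the goal is a conclusion that harm is absent.

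Under Statistical analysis, the change from baseline in each behaviour is calculated at each follow-up and compared between the two arms by t-test or Mann–Whitney U. The section then says "The *p*-values obtained will be corrected according to the Bonferroni criterion", without giving the number of tests, and later "In all cases, a value of *p* less than 0.05 will be considered significant". No within-arm test, largest tolerable increase or confidence limit appears.

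The Sample size section is built on the efficacy comparison only: "an effect size *d* = 0.85, 25 individuals per group are needed", at 80% power and two-tailed, with 29 per group enrolled to allow for 15% loss.

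Under Patient eligibility, every participant must have had a suicide attempt, suicidal gesture or self-injury in the month before entry.

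**The concern.** Safety is named beside efficacy in the Abstract, the General objective and the Discussion. The objective is worded as something to be shown, while the inference provided is a test whose null hypothesis is no difference. Failing to reject that null does not show that it is true, at any sample size. The contrast does not match either: the objective compares app users with their own baseline, and the planned tests compare the arms.

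The multiplicity correction makes this worse for a safety reading. Each added behaviour or visit raises the bar for declaring an increase, so a result of no significant increase becomes easier to reach.

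At stake is a statement about self-injury in high-risk adolescents, for an app already free to download. If a non-significant result were reported as meeting this objective, the data would not support the claim.

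**Working it through.** **1. The plan's own figure.** Inputs from Sample size: d = 0.85, two-sided alpha 0.05, power 80%, Mann–Whitney U. Noncentral-t power with the rank-test efficiency 3/π for normal data needs 24 per arm and gives 82.0% power at 25. The stated 25 reproduces to within one patient, so n = 25 evaluable per arm is used below.

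**2. Family size.** The protocol does not state it. Primary outcome measure lists 5 types of behaviour, and Trial design gives three follow-ups (days 30, 60 and 90). Candidate families are 5 and 5 × 3 = 15, so alpha is 0.05, 0.05/5 = 0.01 or 0.05/15 = 0.0033.

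**3. Planned contrast: between arms, two-sided.** Assume a true increase of 0.5 SD of the change score. The noncentrality is 0.5 × √(25/2) = 1.768 on 48 degrees of freedom. The miss rate is the probability that |T| stays below the critical value.

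| Tests in family | alpha | critical t | miss, 25 per arm | miss, 29 per arm |
|---|---|---|---|---|
| 1 | 0.05 | 2.011 | 59.0% | 53.5% |
| 5 | 0.01 | 2.682 | 80.7% | 76.7% |
| 15 | 0.0033 | 3.089 | 89.4% | 86.5% |

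Mann–Whitney with efficiency 3/π at 25 per arm gives 60.6%, 81.9% and 90.1%.

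**4. The contrast in the objective: within the app arm.** The plan names no such test. For a paired t-test at n = 25 the noncentrality is 0.5 × √25 = 2.5 on 24 degrees of freedom. The two-sided miss rate at 0.05 is 33.0%. A one-sided test at 0.05 has power 78.3%, so it misses 21.7%; at n = 29 it misses 16.3%.

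These lower rates assume that, without an app effect, the expected change is zero. Selection on self-injury in the previous month makes that doubtful. Frequencies would tend to fall from baseline whatever the app does, and a harmful effect would be offset by that fall. TAU participants are selected in the same way, so the between-arm difference does not carry this bias.

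**5. What a confidence limit would show.** With no observed between-arm difference at 25 per arm, the upper one-sided 95% limit is t(0.95, 48) × √(2/25) = 1.677 × 0.2828 = 0.474 SD. Increases up to about 0.47 SD would remain compatible with the data. For an illustrative margin of 0.5 SD and a true difference of zero, the chance that the limit falls below the margin is 54% at 25 per arm; 80% would need about 50 per arm.

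**The case against.** The strongest reply is that the protocol never says a non-significant p-value will be read as safety, and that a condensed article may leave a margin or bound to the full protocol or SAP. The first part stands. A reader might infer that the trial would treat non-significance as proof of safety, but the text supports only that it could. The second part does not dispose of the point. The article states both the objective and the inferential rule, applies the threshold to all cases, and the two do not fit together. That is a matter of what is written, not of missing detail.

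Other safety provisions exist. Data management allows termination if self-harm exceeds expected rates and requires attributable adverse events to be reported; Safety procedure requires an assessment at each interview. These govern conduct. They carry no threshold and give no basis for concluding that frequency did not rise.

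The sizes rest on assumptions, and a directional test is kinder: one-sided at 0.05, the between-arm miss rate at 25 per arm is 46% (1 − 0.539). That is fair, and the figures are illustrations only.

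Three stronger readings are not supported:

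- Running the figures together as a single 33% to 89% range would mix an uncorrected within-arm test that the plan does not name with a between-arm test over an assumed 15 comparisons.
- Judging the miss rates against a 20% limit would borrow the power target of the primary efficacy test; no such limit is set for safety.
- The statement in Ethics and dissemination that "in previous studies we have shown that the app does not increase the risk of suicide" might be taken as the same error. It refers to studies in the plural whose results are not in the document, so how that conclusion was reached cannot be judged here.

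**Conclusion.** The point holds in this form: the objective to establish no increase from baseline has no analysis able to meet it, and the planned between-arm tests of zero difference cannot stand in for one. This conclusion needs no assumed effect size.

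The size is illustrative. For a true 0.5-SD increase and 25 per arm, the planned comparison misses 59% uncorrected, 81% with 5 tests and 89% with 15. These figures assume the 0.5 SD, the family sizes, normal-theory power and equal arms, although simple randomisation may leave the arms unequal. Adding a within-arm test would be a poor remedy because of regression to the mean.

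**What to change.** 1. Reword the objective along these lines: estimate the change in frequency of self-injurious thoughts and behaviours with the app, and the largest increase relative to TAU compatible with the data.
2. Base the safety conclusion on the upper one-sided 95% confidence limit of the app-minus-TAU difference in change, with the within-arm change descriptive only. Report that no increase was detected (where that is so) and that increases up to the limit are not excluded, unless the limit lies below a margin that the investigators fix before any outcome data by arm are analysed. The choice of margin is theirs; the 0.5 SD used above is not a proposal.
3. State that the Bonferroni correction does not apply to the harm analyses.

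The cost is one reworded objective, a short addition to Statistical analysis, and confidence limits from data already being collected. No patients or visits are added. The price is a weaker safety claim, with a limit of about +0.47 SD at 25 per arm if no difference is observed, and more false harm signals once the correction is lifted.

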### Study setting

Young people aged 10 to 19 years (WHO definition of adolescence) who attend a Mental Health Services of the Pedro de Elizalde Children’s General Hospital (in the City of Buenos Aires), and the Children’s Hospital “Sor María Ludovica” from the city of La Plata (Province of Buenos Aires) who have presented some type of self-injurious behavior (with or without suicidal intent) the month before the evaluation will be randomly assigned to one of the arms of study.

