### Patient eligibility

#### Subjects

Patients aged 10 to 19 who attend on as outpatient basis or have been hospitalized in Mental Health Services and who have a smartphone where the application can be installed and used are eligible to participate in the study. In addition, participants must have had suicidal behavior in the 4 weeks before entering the study. The SITBI assessment questions will be used to define suicidal behavior: suicide attempt [“made a suicide attempt (i.e., purposefully hurt yourself with at least some intent to die)?”], exhibited a suicidal gesture (Have you ever done something to lead someone to believe that you wanted to kill yourself when you really had no intention of doing so?) or self-injurious behavior (Have you ever done something with the purpose of hurting yourself without wanting to die?–for example, cutting or burning-) in the last month before entering the study (53, 54).

The participant must have plans to continue treatment in the next 3 months, have the ability to provide assent/consent for cognitive or language reasons, and the functional capacity to use the application, which will be operationally determined by a score above 30 on the Self-Care motor domain, above 10 on the Communication cognitive domain and above 14 on the Cognitive domain of Social Knowledge in the Functional Independence Measurement scale (46).

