### Data management

All research data collected in this trial will be stored using a unique participant ID code, and will be stored in numerical order and stored in a secure and accessible place and manner in the Institute of Pharmacology od the School of Medicine of the University of Buenos Aires. Participant files will be maintained in storage for a period of 3 years after completion of the study.

The data manager will be responsible for uploading the collected data to a secure database, and will be responsible for securely transferring data to the research team. Data will be exported into appropriate statistical software for analysis. Only authorized study team members are able to view data. If there a rationale (e.g., participant request, unexpected adverse events, aggregate data indicates self-harm above the rates expected from this group) the research team will make the decision to terminate the trial if necessary. All adverse events attributable to a study intervention will be recorded and reported to the ethics committee of each institution. Participants may be withdrawn from the study if they experience a serious adverse event that is attributable to a study intervention or procedure, or means they can no longer participate in the study. Participants may also self-withdraw consent to take part. Participants that are withdrawn from the study will not be replaced.

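### The safety objective compares app recipients with their own baseline, in a sample selected for recent self-injury, instead of using the randomised comparison already planned

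*Protocol article*

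**What the plan says.** The general objective covers efficacy, safety and acceptability. Under Secondary specific objectives, one item is worded as absence of harm: it aims to show that self-injurious thoughts and behaviours do not become more frequent "in those participants who receive the application compared to the baseline levels at study onset". The comparator is the app arm's own starting level; TAU is not mentioned in that item.

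Entry depends on a recent event. Study setting describes patients "who have presented some type of self-injurious behavior (with or without suicidal intent) the month before the evaluation", and Subjects repeats that "participants must have had suicidal behavior in the 4 weeks before entering the study". Under Trial design, both arms continue the hospital's usual treatment throughout.

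On adverse events, Data management says: "All adverse events attributable to a study intervention will be recorded and reported to the ethics committee of each institution".

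Other parts of the article do compare the arms. The primary objective is to "Compare the change in the frequency of self-injurious behaviors in the participants who receive the app" against that of participants without it. The first secondary objective does the same for thoughts, and the last compares time to psychiatric admission. Participant timeline plans the SITBI at baseline and at days 30, 60 and 90, and asks about hospitalisation, without restriction to one arm. Statistical analysis compares change from baseline between the groups for each behaviour at each follow-up.

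**The concern.** A group chosen because something happened in the last month will, on average, show less of it in the next month, with or without an effective intervention. Usual treatment can lower the frequency further. A fall or a flat line in the app arm therefore says little about whether the app is harmless, because the relevant question is what would have happened without it. In a randomised trial the TAU arm answers that question, and the safety objective as worded leaves it aside.

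The verb is a second problem. Establishing that there is no increase is a positive claim. A non-significant pre-post test in a small arm does not support it.

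The adverse-event sentence has a related weakness. TAU participants receive no app, so few of their events could be attributed to a study intervention. A record limited to such events could not be compared fairly between arms.

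At stake is a statement that a freely downloadable app is safe in high-risk adolescents, resting on a comparison that tends to look reassuring.

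**Working it through.** **Sample size, for context.** The article states 25 per group (d = 0.85, two-sided 5%, 80% power, Mann–Whitney), raised to 29 for 15% loss. The noncentral t calculation with the Mann–Whitney efficiency adjustment gives 24 per group for a normal parent (power 82.0% at 25) and 27 under the minimum-efficiency option (77.9% at 25). 25 × 1.15 = 28.75, so 29; dividing instead, 25 / 0.85 = 29.4, so 30. The stated figures reproduce closely. They bear on this point only by showing that about 25 people per arm would be analysed.

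**Regression to the mean: assumed model.** The article gives no event rates, so the inputs are assumptions. Each person has a stable monthly rate, gamma-distributed with mean m and shape k. The 30-day count is Poisson, and entry requires a count of at least 1. Then:

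- P0 = (k/(k+m))^k is the chance of no event.
- P1 = m·(k/(k+m))^(k+1) is the chance of exactly one.
- Baseline mean among those enrolled: B = m/(1 − P0).
- Follow-up mean with no app effect: F = (m − P1)/(1 − P0).
- Expected fall: 1 − F/B = (k/(k+m))^(k+1).
- Harm rate ratio that just returns the arm to baseline: B/F.

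Worked case, m = 1 and k = 1: P0 = 0.5, so B = 1/0.5 = 2.0. P1 = 0.25, so F = 0.75/0.5 = 1.5. The fall is 25%, and B/F = 1.33. An app that raised the rate by a third would look unchanged from baseline.

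Expected fall with no effect (masked rate ratio in brackets):

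| Mean per month | k = 0.5 | k = 1 | k = 2 |
|---|---|---|---|
| 0.5 | 35% (1.55) | 44% (1.80) | 51% (2.05) |
| 1 | 19% (1.24) | 25% (1.33) | 30% (1.42) |
| 2 | 9% (1.10) | 11% (1.13) | 13% (1.14) |
| 4 | 4% (1.04) | 4% (1.04) | 4% (1.04) |

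Any effect of usual care would add to these falls.

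**What 25 per arm would show.** Simulation with k = 1, 500 trials per setting and unadjusted two-sided 5% tests. The within-arm test is a Wilcoxon signed-rank test (assumed, since the article names none); the between-arm test is Mann–Whitney on change. Simulation error is at most about √(0.25/500) = 2.2 percentage points.

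- No app effect: the app arm shows a significant fall from baseline in 42% of trials at mean 1, and in 14% at mean 2.
- Rate ratio 1.5, mean 1: a significant rise from baseline in 5% of trials; the between-arm test detects harm in 26%.
- Rate ratio 1.5, mean 2: 34% against 39%.
- Rate ratio 2: 39% against 70% at mean 1; 87% against 84% at mean 2.

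At mean 1, then, about 95% of trials of an app that raises the rate by half would show no significant rise from baseline. The gap between the two tests closes as the underlying rate rises.

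**The case against.** The strongest reply is that the harm of most interest is already compared with TAU. Self-injurious behaviours, thoughts and admissions are collected in both arms, change is compared between arms, and the sizing test is two-tailed, so harm can appear in the primary result. Statistical analysis describes no within-arm test at all. A reader might infer that no comparison with TAU is possible; that is not so. What stands is that the objective named for safety does not use that comparison. Two limits also apply. Power for moderate harm is low even before the planned Bonferroni correction. And the Cox model in Statistical analysis is described for readmission in patients enrolled while hospitalised, which is narrower than the admission objective.

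The size is also open to challenge. Entry needs any one of an attempt, a gesture or self-injury, while the analysis is per behaviour, and thoughts are not an entry criterion. The model selects on the same count that it then analyses, so it will not match every planned variable. At 4 events per month the fall is only about 4%. This is fair: the direction is secure for the behaviours that drive entry, but the amount is not known.

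Three further inferences lack support:

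- That non-attributable events go unrecorded. The article does not say so, and a full protocol may add detail. The sentence needs clarifying because of what it leaves open.
- That unblinded developers decide attribution. The article names no one for that task.
- That withdrawal removes the worst app-arm outcomes. The article says "Participants may be withdrawn from the study if they experience a serious adverse event that is attributable to a study intervention or procedure". This is permissive, and it covers procedures as well as the intervention. The rule also extends to events that prevent further participation, so it can apply in either arm. Missing frequencies are to be multiply imputed.

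**Conclusion.** The point holds as a fault in how the safety objective is framed. Followed as written, it could support a conclusion of no increase when the app does harm relative to TAU, because participants are selected on a recent event and remain in treatment. Under the assumed gamma-Poisson counts, selection alone produces a fall of about 4% to 51%, which would hide a true rate ratio of about 1.04 to 2.05. The range depends on event rates that the article does not give. Independently of those rates, a non-significant change in about 25 people cannot establish absence of harm. The data for a valid comparison are already planned, so the fault lies in the objective and in the adverse-event wording, not in the trial's ability to compare the arms.

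**What to change.** Restate the secondary safety objective as app versus TAU. For self-injurious thoughts, behaviours, attempts and psychiatric admissions, report the between-arm difference or rate ratio with its 95% confidence interval, and name the limit in the direction of harm. Include all randomised participants in the admission comparison, not only those enrolled as inpatients. Pre-post change in the app arm may be described, but no conclusion of no increase should be drawn from it.

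In Data management, state that serious adverse events are recorded in both arms whatever the attribution.

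The cost is small: revised wording, a few extra estimates from data already planned, and a short serious-event log in both arms. No assessment is added. The downside is that the intervals will be wide at this sample size, so the trial may be unable to exclude moderate harm. The report should say so.
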